**Adhering to the 2019 Canada's Food Guide recommendations on healthy food choices, including extra protein^i^**																
	Male individuals	6	1.5	1.5	3.5	1.5	1	No change		Minimum		Minimum	Minimum		No change	
	Female individuals	5	1.5	1.3	3.0	1.5	1	No change		Minimum		Minimum	Minimum		No change	
**Adhering to the 2019 Canada's Food Guide recommendations on healthy food choices, including extra protein and physical activity**																
	Male individuals	6	1.5	1.5	3.5	1.5	1	No change		Minimum		Minimum	Minimum		30 or more	
	Female individuals	5	1.5	1.3	3.0	1.5	1	No change		Minimum		Minimum	Minimum		30 or more	

^a^The emulation of all hypothetical interventions will be implemented using a substitution approach in statistical models. In all models, 1 variable for total food intake and 1 variable for total beverage intake will be included, and foods not recommended will be left out from the models (ie, non–whole grain foods; other low nutritive value foods; juice, sugary drinks and alcohol; and fatty foods rich in saturated fats).

^b^RA: reference amount.

^c^Dietary supplements were not intervened on but were, nonetheless, excluded from foods and beverages not recommended to avoid being considered in the substitution. In other words, participants would not be instructed to modify their dietary supplements in the hypothetical trial.

^d^Minimum indicates that consumption would be set at the smallest amount, permitting a concomitant increase in recommended foods to meet Canada’s Food Guide targets. Portions for foods not recommended may vary on an individual basis.

^e^Physical activity corresponds to aerobic exercise of moderate or higher intensity [6].

^f^Values will be the averages observed at baseline in the NuAge cohort. In other words, values will be the observed intakes for the food categories or amount of physical activity when no change is applied.

^g^Not applicable.

^h^Values are derived from Health Canada’s simulated composite diets of adults aged ≥71 years. Participants would be expected to meet these targets for each food category. The specific food choices within these categories would be at the participants’ discretion. Values for vegetables and fruits, whole grain foods, and plant-based protein foods were truncated to correspond, at most, to the 90th percentile of the distribution of usual intakes among Canadians aged 65 years in 2015.

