#### Implementation

In the target trial, the sustained intervention strategy could be implemented as follows:

Step 1: the participants’ usual dietary intake and physical activity would be assessed by research dietitians at each study visit.Step 2: if reported food intakes and duration of physical activity were equal to or above the prespecified thresholds (Table 2), no change would be suggested to the participants’ diet or physical activity. If food intakes or duration of physical activity were below the prespecified thresholds, participants would be instructed to increase food consumption to exactly the prespecified portions or increase physical activity duration to 30 minutes per day (when applicable).Step 3: if changes are required, participants would be instructed to decrease consumption of foods not recommended by the same amount as the increase in step 2. For example, if a 2-serving increase in vegetables and fruits is required to meet the prespecified intervention thresholds, participants would be instructed to substitute 2 servings of vegetables and fruits for non–whole grain foods; other low nutritive value foods; juice, sugary drinks and alcohol; and fatty foods rich in saturated fats.

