In the emulation, for all hypothetical interventions, substitution will be implemented by including total intakes as a covariate and excluding foods not recommended from the models. More precisely, a variable reflecting total food intake (in RA/d) and a variable reflecting total beverage intake (in RA/d) will be included in all models. Hence, total food and beverage intakes will be constant across hypothetical diet interventions. In this approach to account for total energy, all model coefficients reflect the action of increasing intakes of recommended foods and a concomitant decrease in *any* of the foods not recommended [32]. On one hand, this approach can be potentially confusing [17,33], as the default interpretation of model coefficients assumes increasing the intake of each *food included in the model* while simultaneously decreasing the intake of foods *excluded from the model* [32]. On the other hand, the standard model is generally consistent with the implementation of dietary intervention in feeding trials [16,36,37]. The standard model also reduces the number of variables to be considered as intervention variables. Otherwise, 4 additional dietary components would have to be modeled for foods not recommended (ie, non–whole grain foods; other low nutritive value foods; juice, sugary drinks and alcohol; and fatty foods rich in saturated fats). Finally, the explicit description of the intervention strategies in the target trial protocol clarifies the estimand of interest, as done in an earlier study [19,31].

Notably, nutrient-based recommendations in CFG (ie, saturated fats, free sugars, and sodium intake) are not explicitly modeled to avoid the problems associated with mixed-unit models [17]. In the target trial, we assume that nutrient-based targets would be met by reducing consumption of foods not recommended (ie, non–whole grain foods; other low nutritive value foods; juice, sugary drinks, and alcohol; and fatty foods rich in saturated fats). In that regard, food-level substitution analyses in Canadians support this assumption for saturated fats [38,39].

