### Assignment

We will attempt to emulate random allocation or randomization by adjusting for dietary intakes in the year before the intervention, as well as adjusting for covariates at the start of the study. Covariates were identified using the causal diagrams depicted in Figure 1, based on background knowledge of the relationship between the hypothetical lifestyle intervention and outcomes.

Dietary components that are the foundation for healthy eating in CFG include intakes of vegetables and fruits, whole grains, protein foods (plant- and animal-based protein foods, milk, and plant-based beverages with protein), and unsaturated oils and fats [1].

Covariates, including age at baseline, biological sex, region, education, living alone, smoking and drinking (alcohol) habits, major chronic diseases (ie, hypertension, diabetes, cancer, and heart disease), the number of medications, supplement use (eg, vitamins and minerals), and height and weight, are as follows:

*Z*, baseline covariates: age, sex, region, education, history of smoking, height, and former cancer history*P*, previous exposure (ie, exposure of time-varying intervention before baseline): dietary habits before baseline*L*, (time-varying) covariates: weight, number of medications, supplement use, living alone, major chronic diseases (eg, hypertension, diabetes, cancer, and heart disease), and smoking and alcohol habits*X*, (time-varying) treatment: diet and physical activity habits*Y*, end of follow-up outcome: muscle health, general health, and cognitive health

Contrary to dietary habits, data on physical activity habits before baseline were not collected in NuAge. In this case, the potential effect of previous physical activity habits will not be accounted for in the models that aim to emulate the sustained physical activity intervention strategy. For the models emulating the sustained diet intervention strategy only, physical activity habits during the study will be used as a covariate, hence mitigating the confounding of previous physical activity, at least to some extent.

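### Alcohol is both a displaced item and an adjustment covariate, and two separate intake totals stop foods from displacing drinks, so the modelled substitution is not the one described

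*Protocol article*

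**What the plan says.** All references are to the Protocol article.

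- **Alcohol as a displaced item.** Table 2 marks sugary drinks and alcohol as *Minimum* in each of the three active strategies. Footnote a states the modelling device: "foods not recommended will be left out from the models (ie, non–whole grain foods; other low nutritive value foods; juice, sugary drinks and alcohol". Fats high in saturated fat complete its list.
- **Alcohol as a covariate.** The Assignment section lists the time-varying covariates L, ending with "major chronic diseases (eg, hypertension, diabetes, cancer, and heart disease), and smoking and alcohol habits".
- **The only stated exemption.** Footnote c takes dietary supplements out of the not-recommended group so that they do not enter the substitution. Supplements are also in L, and Table 2 marks them *No change*. Nothing similar is said of alcohol.
- **Two totals.** Under Implementation, "a variable reflecting total food intake (in RA/d) and a variable reflecting total beverage intake (in RA/d) will be included in all models". From this the article concludes: "Hence, total food and beverage intakes will be constant across hypothetical diet interventions".
- **Target trial rule.** In Step 3, "participants would be instructed to decrease consumption of foods not recommended by the same amount as the increase in step 2". The example has participants "substitute 2 servings of vegetables and fruits for non–whole grain foods; other low nutritive value foods; juice, sugary drinks and alcohol". Its list closes with the same group of fats.
- **Reading of the coefficients.** Under Implementation, "all model coefficients reflect the action of increasing intakes of recommended foods and a concomitant decrease in". The object of that decrease is given as *any* item in the not-recommended group.

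**The concern.** A substitution model of this kind displaces whatever is left out of it while the total is held. Anything put back in as a covariate is held constant and is no longer displaced. Alcohol appears on both sides of that line, and the text does not say which role prevails.

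The second problem is independent of alcohol. With a food total and a beverage total both in the model, a food cannot be exchanged for a drink. Yet the Step 3 example takes a vegetable and fruit increase out of a pool that includes drinks, and the sentence on coefficients promises displacement from the whole omitted group.

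What is at stake is the meaning of the estimate. The article relies on its explicit description of the strategies to make the estimand clear, and says elsewhere that the handling of total intake must match the research question. A reader would take the result for the food guide strategy to include reductions in sugary drinks and alcohol that the models impose only in part.

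**Working it through.** The plan states no figure on this point, so there is none to reproduce. The check uses the Table 2 targets and the algebra of the described model.

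**Table 2 totals (RA/d)**

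- Food guide strategy, foods: males 6 + 1.5 + 1.0 + 2.0 + 1 = 11.5; females 5 + 1.5 + 0.8 + 1.5 + 1 = 9.8. Milk and plant-based beverages: 1.0.
- Extra-protein strategies, foods: males 6 + 1.5 + 1.5 + 3.5 + 1 = 13.5; females 5 + 1.5 + 1.3 + 3.0 + 1 = 11.8. Beverages: 1.5.
- The increments (2.0 for foods, 0.5 for beverages) agree with footnote i.

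**Model.** Let R be recommended foods, N non-recommended foods, M milk, S juice and sugary drinks, and A alcohol, with effects bR, bN, bM, bS and bA. The totals are TF = R + N and TB = M + S + A.

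1. *Food coefficient.* Putting N = TF − R gives bR − bN. Neither bS nor bA appears, so this is a food-for-food swap only.
2. *Milk coefficient with alcohol as a covariate.* Putting S = TB − M − A gives bM − bS, which is milk for sugary drinks only.
3. *Milk coefficient with alcohol left out.* It is a blend, (1 − w)(bM − bS) + w(bM − bA). With independent intakes, w = var(A) / [var(A) + var(S)].

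**Illustration.** All values here are assumed and none comes from the document. Effects per RA/d are bR = 0.2, bN = −0.3, bM = 0.3, bS = −0.2 and bA = −0.6. Intakes are independent gamma variables with var(A) = 2 × 0.4² = 0.32 and var(S) = 2 × 0.5² = 0.50, so w = 0.32/0.82 = 0.39.

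- Food: 0.2 + 0.3 = 0.50. Least squares on 400,000 simulated people gave 0.50 with or without alcohol, for bA from −0.2 to −1.0.
- Milk, alcohol left out: 0.61 × 0.50 + 0.39 × 0.90 = 0.66; simulated 0.66. For bA of −0.2, −0.4, −0.6 and −1.0 the simulated values were 0.50, 0.58, 0.66 and 0.81.
- Milk, alcohol included: 0.3 + 0.2 = 0.50; simulated 0.50 to 0.51 throughout.
- If total beverages also contains drinks with no effect, such as water or tea, the milk coefficient falls to 0.36 without alcohol and 0.32 with it. The document does not say what the beverage total contains.

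**Over time.** The g-formula simulates L under each strategy. In a two-period example with alcohol ordered before milk at each visit and an assumed weak association, raising mean milk by 0.22 RA/d left same-visit alcohol unchanged and moved next-visit alcohol by −0.01.

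**Bound on drink displacement.** Milk is the only beverage with a target, so the directly imposed reduction in other drinks per visit is max(0, target − milk intake). That is at most 1.0 RA/d in the food guide strategy, at most 1.5 RA/d in the extra-protein strategies, and 0 for anyone at the milk target.

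**Side by side with Step 3.** Take a hypothetical woman at the milk target of 1.0 who eats 3 RA/d of vegetables and fruits against a target of 5. Step 3 takes the 5 − 3 = 2 RA/d from a pool that includes drinks. The two-total model takes all 2 from non-recommended foods and 0 from drinks.

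**The case against.** Several parts of the opposing case stand.

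- **Fixing total beverages does not protect drinks.** A reader might infer that it does. The reverse is true: holding that total is what makes milk displace the omitted drinks. The mismatch comes from having two totals.
- **Alcohol displacement is not shown to be zero.** That inference needs the covariate to measure the same intake as alcohol in RA/d, and to precede treatment at every visit. The Assignment section pairs alcohol with smoking as habits, which fits a coarse status variable. The ordering after baseline would be in Figure 2, which is not shown here. The section on modelling of hypothetical interventions also says that feedback between intervention and confounders is handled, so alcohol is not frozen across visits.
- ***Minimum* is not a free-standing reduction target.** Footnote d ties it to the room needed for recommended foods, and Step 2 suggests no change for someone at or above every threshold. For such a person the model and the target trial agree. They can part only for people short of at least one food target, or through the alcohol covariate for people short of the milk target.
- **Step 3 does not fix the split among displaced items.** It describes how the strategy could be implemented, and cutting foods only would satisfy the equal-amount rule. The two totals are also openly stated.

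The last argument softens the conflict but does not remove it. The example names drinks among the items a food increase may replace, the models rule that out, and the coefficient sentence covers the whole omitted group. Nor does a coarse alcohol variable dissolve the double role; it only reduces the overlap.

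**Conclusion.** The concern holds in two parts. First, alcohol has two unreconciled roles. As far as the covariate tracks the same intake and is ordered before treatment, adjusting for it takes alcohol out of the same-visit substitution and leaves only modelled association at later visits. Second, the two-total models estimate foods for foods and beverages for beverages. The sentence covering *any* food not recommended is therefore untrue as written, and the Step 3 example is not what is estimated. Directly imposed drink displacement is at most 1.0 or 1.5 RA/d, depending on strategy; that bound follows from Table 2 alone.

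A reader might go further and conclude that effects on blood pressure, glucose, waist circumference or cognition are biased by a known amount. The document does not support this. It gives no intakes of alcohol, sugary drinks or milk and no effect sizes, so neither size nor direction can be derived, and the coefficients above show only the mechanism. Those outcomes are also secondary; no consequence for the primary outcomes of muscle strength and physical function has been shown.

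**What to change.** 1. State whether alcohol belongs to the substituted set or is a confounder held out of it, as footnote c does for supplements. Define the alcohol covariate (status, frequency or RA/d), its place in the ordering at each visit, and what total beverages contains. Report results with and without time-varying alcohol in L, keeping pre-baseline alcohol in P as far as the food-frequency questionnaire records it. The version without it may carry residual confounding by later drinking. For that reason both are reported, and outright removal of alcohol from L is not asked for.
2. Reconcile Step 3 and the coefficient sentence with the two-total models: say that foods displace foods and beverages displace beverages, and interpret the effects as that substitution. A single combined total could be added as a sensitivity analysis. It is optional, since it estimates a different substitution.

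The cost is some wording and one additional set of model runs with their bootstrap replicates. No new data are needed.

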**Figure 1 figure1:**
[figure not shown]
Causal directed acyclic graph (DAG) depicting (A) confounding and (B) successful emulation of randomization using g-methods at baseline between the intervention strategy (X) and outcome (Y). Baseline covariates (both time-invariant [Z] and time-varying [L]) and previous diet and physical activity habits (P) must be considered to emulate randomization. Time-varying treatment and covariates are not shown in this DAG to focus on randomization emulation. Subscripts indicate the time points, where 0 represents baseline.

A successful emulation of randomization requires that there is no unmeasured confounding. However, this is never guaranteed with observational data. Thus, we emphasize our assumptions that (1) the causal graph accurately depicts the relationship under study and (2) the covariates included are a sufficient set of covariates to address confounding.

### Outcomes

The primary outcomes will be the mean end of follow-up values for muscle strength (ie, handgrip using vigorimeter, elbow flexor, and knee extensor) and physical function (ie, normal and fast walking and “timed up-and-go”). Outcome values were measured according to a standardized protocol in NuAge [25].

For secondary outcomes, mean end of follow-up values for a set of relevant variables will be considered by domains:

*General health:* waist circumference, blood pressure (systolic and diastolic), blood glucose, and estimated glomerular filtration rate*Cognition:* the modified Mini-Mental State Examination score

### Time Zero and Follow-Up

In the target trial of a sustained lifestyle intervention, participants would be met at baseline and then regularly to ensure that diet and physical activity habits are consistent with the intervention assigned by the random allocation. The hypothetical diet and physical activity intervention would be assigned and initiated at baseline. In the emulation, annual follow-ups with comprehensive diet, physical activity, and covariate data collection are available to emulate the hypothetical intervention. Hence, participants would be followed from the study baseline (time point 0; ie, the time at which the intervention strategy would also be assigned and would begin), at each year (ie, time points 1 and 2), and until the end of the study (time point 3). We also assume that the diet and physical activity habits measured at each follow-up time adequately reflect the habits during the entire year.

The end of follow-up outcome measurements will be used to estimate the effect of the sustained lifestyle intervention strategy. Measures of dietary intake and physical activity throughout the study (ie, time point 0 to time point 3) will be used to emulate the sustained lifestyle intervention. Dietary intakes in the year preceding the intervention will be estimated using the frequency questionnaire completed at baseline (ie, time point 0). Missing covariate data at a given follow-up will be carried forward once, after which participants will be considered as having incomplete follow-up.

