Interventions^b^	Each individual would be assigned to 1 of the 4 following strategies: Control group (habitual diet, ie, typical North American diet) Adherence to Canada’s Food Guide recommendations on healthy food choices Adherence to Canada’s Food Guide recommendations on healthy food choices and including a high-protein reformulation Adherence to Canada’s Food Guide recommendations on healthy food choices, including a high-protein reformulation and a minimal physical activity component Each strategy is followed until the end of follow-up. Participants assigned to a lifestyle strategy are expected to maintain their dietary intake or amount of physical activity at or above the prespecified threshold by the corresponding intervention strategy.	The intervention component will be the same as that specified in the target trial. Furthermore, we will assume that each dietary assessment period (ie, within 2 months beginning at each time point) accurately reflects the average diet in the interval between follow-ups.
Assignment	Participants are randomly assigned to a dietary strategy but are not blinded to their assignment.	We will attempt to emulate randomized assignment by adjusting for dietary intakes before baseline and baseline covariates.
Outcomes	The outcomes are physical function and muscle strength, general health indicators, and cognitive health.	The outcomes will be physical function and muscle strength, general health indicators, and cognitive health.
Time zero and follow-up	The study starts at baseline and ends at incomplete follow-up or 3 years after baseline, whichever occurs first.	The study will start at baseline and end at incomplete follow-up or 3 years after baseline, whichever occurs first. An incomplete follow-up is defined as missing data for questionnaires (nonresponse or loss to follow-up) or missing outcome data at the end of follow-up.
Causal contrast^c^	Intention-to-treat effect Per-protocol effect	Observational analog of both contrasts: Secondary: intention-to-treat effect Primary: per-protocol effect

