### Causal Contrast

The estimand of interest in this study, the target causal effect of a sustained lifestyle intervention strategy, is

*E*(*Y*^1,1,1,1^|*C* = 0) – *E*(*Y*^0,0,0,0^|*C* = 0) **(1)**

that is, the expected value of a given health outcome *Y* at the end of follow-up if all participants had increased their adherence to CFG recommendations on healthy food choices and physical activity, when applicable, at all 4 time points (*X_k_=1*, *always intervene*) versus if all participants had maintained their habitual diet and physical activity (*X_k_=0*, *never intervene*). The estimand (equation 1) also indicates that all participants completed the intervention (C=0), that is, in the absence of incomplete follow-up.

The causal contrasts of interest are the observational analogs of intention-to-treat and per-protocol analyses [11]. Given the observational design, participants are not expected to have followed a treatment strategy unknown to them at the time of data collection. Therefore, the primary analysis will be the per-protocol contrast of a sustained lifestyle intervention strategy. In the per-protocol analysis, nonadherence to the hypothetical interventions can be accounted for. In the target trial, participants with a condition after baseline that would have prevented or limited participation in a hypothetical lifestyle intervention would be allowed to discontinue the intervention (eg, lengthy hospitalization, prolonged bed rest, and incident cancer). In the emulation, if such conditions occur in a sufficiently large number of participants, these participants will be “excused” from following the hypothetical intervention [23]. In other words, participants who would have been unable to pursue the study due to major events will not be considered as having incomplete follow-up if they attended the annual assessment. Allowing participants to discontinue adhering to the hypothetical intervention strategy mitigates confounding by the disease burden [23].

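### Equation 1 intervenes at four time points, but only three yearly intervals precede the time point 3 outcome, so exposure before outcome is not secured for the last exposure in the primary contrast

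*Protocol article*

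**What the plan says.** All references are to the Protocol article.

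- **Exposure waves.** Time Zero and Follow-Up states: "Measures of dietary intake and physical activity throughout the study (ie, time point 0 to time point 3) will be used" to emulate the sustained strategy.
- **Estimand.** Causal Contrast defines equation 1 as the contrast of Y^{1,1,1,1} with Y^{0,0,0,0}, with the strategy applied "at all 4 time points".
- **Follow-up and outcome.** Table 1 states: "The study will start at baseline and end at incomplete follow-up or 3 years after baseline, whichever occurs first". Time Zero and Follow-Up labels that end as time point 3, and Outcomes takes the end-of-follow-up value of each measure.
- **Diet timing.** Table 1 assumes that "each dietary assessment period (ie, within 2 months beginning at each time point) accurately reflects the average diet in the interval between follow-ups". Time Zero and Follow-Up adds that habits recorded at a visit stand for a whole year, without saying whether it is the year before or the year after.
- **Start of the strategy.** It is assigned and begins at time point 0. Diet in the year before is a separate variable, P, taken from the food-frequency questionnaire (Assignment; Dietary Assessment).
- **Activity timing.** Physical Activity Assessment names the questionnaire but does not place it before or after the outcome tests.

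**The concern.** A sustained-strategy contrast has a causal reading only if each exposure in it comes before the outcome. The fourth exposure shares its time point with the outcome, and for diet the recording window opens there and runs forward.

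The primary outcomes are strength, walking speed and timed up-and-go. A participant's physical state at the last visit could plausibly alter the diet or activity reported at that visit. If it does, an outcome model that includes the last exposure would count part of that association as an effect of the strategy.

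The planned checks would not reveal this. The model check compares observed with predicted time-varying covariates, and the measurement-error comparison uses baseline intakes only (Discussion, Principal Findings; Sensitivity Analysis to Assess the Impact of Measurement Error). Temporal order is not among the key assumptions listed in the Discussion, although the Introduction warns against a misaligned time zero.

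**Working it through.** The plan gives no figure on this point to reproduce. The check is a count, followed by an illustration.

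**Count.** Follow-up is 3 years with annual visits, so the intervals before the outcome are 0–1, 1–2 and 2–3: three. Equation 1 has four interventions. 4 − 3 = 1 intervention has no interval of its own before the outcome.

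**Does either direction of the whole-year assumption fit all four waves?**

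| Wave | If it stands for the following year | If it stands for the preceding year |
|---|---|---|
| X_0 | year 1 | year before baseline, already P |
| X_1 | year 2 | year 1 |
| X_2 | year 3 | year 2 |
| X_3 | year 4, after the outcome | year 3 |

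Neither does. The rest of the protocol points to the forward reading: the strategy begins at time point 0, the questionnaire covers the prior year, and the intention-to-treat analog treats baseline habits as a point intervention. Under Implementation, intake is assessed at a visit and changes are then instructed. An instruction issued at the last visit has no time to act on an outcome taken at that visit.

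**Illustration of size.** All inputs are assumptions; the documents give none of them. There is one exposure, measured without error, with SD 1 and autocorrelation 0.6. Y has SD 1 and does not depend on any exposure. X_3 = 0.6·X_2 + a·Y + e, where a is the feedback from Y and Var(X_3) = 1.

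- Var(X_3 given X_2) = 1 − 0.6² = 0.64.
- In the regression of Y on X_0 to X_3, the coefficient of X_3 is a/0.64 and that of X_2 is −0.6·a/0.64. Those of X_0 and X_1 are 0.
- The apparent effect of +1 SD at all four points is (1 − 0.6)·a/0.64 = 0.4·a/0.64.

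| a | 0.4·a/0.64 (SD) | With X_0 to X_2 only |
|---|---|---|
| 0 | 0.00 | 0.00 |
| 0.1 | 0.06 | 0.00 |
| 0.2 | 0.13 | 0.00 |
| 0.3 | 0.19 | 0.00 |
| −0.2 | −0.13 | 0.00 |

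A simulation (n = 400,000) that fixed the SD of e at 0.8, so that the denominator becomes 0.64 + a², gave 0.06, 0.12 and 0.17 for a = 0.1, 0.2 and 0.3. With a true effect of 0.15 SD (0.05 at each of X_0 to X_2), four waves gave 0.15, 0.21, 0.26 and 0.30 for a = 0, 0.1, 0.2 and 0.3. Three waves gave 0.15 in every case.

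**The case against.** The best defence is that the recording date is not the exposure date. The protocol treats each measurement as a proxy for a year of habits, so X_3 may stand for the year before the outcome. This is fair as far as it goes, but it moves the problem to X_0, which would then describe the year already covered by P.

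A reader might go further and infer that part of the estimated effect is reverse causation, appearing as a benefit. The documents do not support that:

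- Feedback from outcome status to reported habits is plausible, but nothing shows that it occurs. With none, the bias is zero.
- The direction is open. Secondary outcomes include glucose, blood pressure and waist circumference, where a poor value could prompt better habits and reverse the sign.
- For diet, the text places the window at and after time point 3. For activity, the order within the visit is not stated.
- Time point 3 covariates in the outcome model would be an inference. The text names only diet and activity for time points 0 to 3.

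The illustrated sizes are also not estimates for this study. The protocol uses threshold interventions that move only those below target, several foods under substitution, covariate adjustment and error-prone recalls. At an assumed reliability of 0.5, the figures fall to about 0.03, 0.07 and 0.10 SD. Participants with major events may also be excused from the strategy if there are enough of them, which could weaken an illness pathway.

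Finally, X_3 is not worthless. Where recalls carry random error, a fourth correlated measure adds slightly to what is known of habitual intake. At reliability 0.5, with no feedback and a true effect of 0.15, four waves recover about 0.11 and three about 0.10. These points limit the claim but do not answer the count of four exposures against three intervals.

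**Conclusion.** The point holds as a defect in the primary estimand. Equation 1 has one intervention more than a strategy starting at time point 0 can place before the outcome, and neither direction of the whole-year assumption accommodates all four waves. Exposure before outcome is therefore not secured for the last exposure, and reverse causation cannot be excluded from the primary per-protocol contrast.

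Its size and sign are unknown. The range of about 0.06 to 0.19 SD depends on the assumed feedback (0.1 to 0.3 SD), autocorrelation of 0.6 and a single error-free exposure. It is zero without feedback and negative if the feedback reverses. The structural conclusion needs only the protocol's own time points. The secondary intention-to-treat analog uses baseline exposure alone and is not affected.

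**What to change.** - In Causal Contrast, restate equation 1 as E(Y^{1,1,1} | C = 0) − E(Y^{0,0,0} | C = 0), with interventions at time points 0, 1 and 2, and amend the text on the number of time points to match.
- In Table 1 and in Time Zero and Follow-Up, state that each assessment represents the year that follows it, so that the time point 3 outcome closes the interval that starts at time point 2.
- Keep time point 3 exposures, and any time point 3 covariates, out of the primary outcome model.
- Report the four-time-point version as a sensitivity analysis, with a note that the order of exposure and outcome at time point 3 is not secured.

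**Cost.** No new data are needed. One noisy exposure wave, with slight extra information on habitual intake, is given up in the primary analysis. The primary estimand would change after the main analysis began in May 2024, so the change and its reason should be disclosed.
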